### Sample/participants

#### Participants

The patients will be recruited from the Oncology Hospitalisation Unit at the CAUSA, and must meet the following selection criteria: A) Inclusion criteria: Participants must have a pathological diagnosis of an oncological disease, be over 18 years of age, be hospitalised at the time of recruitment in the Oncology Unit at CAUSA, meet dyspnoea parameters of 2 or more points on the Medical Research Council scale (MRC), receive fewer than 85 points on the Barthel Index, and have signed an informed consent form indicating voluntary agreement to participate in the study. B) Exclusion criteria: not having an adequate cognitive state to be able to comprehend and follow the orders provided (fewer than 23 points on the Mini Mental State Examination, MMSE), having a haemoglobin level lower than 10 g/dL, being an active smoker at the time of recruitment. C) Withdrawal criteria: disease progression which brings the patient to a terminal situation or to death, and non-completion of the follow-up and final assessments.

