#### Sample size

The sample size has been estimated based on the potential modification of the most stringent of the principal variables of the study—the score on the Barthel Index. For this, as a reference, we have used the results obtained in a study with similar characteristics, in which the scoring on the Barthel Index was modified by 7.5 points [17]. With these premises, accepting an alpha risk of 0.05 and a beta risk of 0.2 in a bilateral contrast, we will need 25 subjects in the first group and 25 subjects in the second group in order to detect a difference greater than or equal to 7.5 units. The assumed common standard deviation is 8.3. We estimate a rate of 20% lost to follow-up. The sample size was estimated using the programme EPIDAT 4.2.

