### Procedures and data collection

#### Evaluations and study plan

Three assessments will be completed in this study: one at the beginning, another after 7 days, and a final one before the patient is discharged from hospital. After recruitment and before randomisation and assignment to the corresponding group, all individuals will complete a baseline assessment (BA), which includes recording the independent variables and the variables of the primary and secondary results of the study. Then, while the patients are still in hospital, the subjects will be randomly assigned to the control or the experimental group, with the corresponding intervention applied in each of them. Later, two more assessments will be completed, one after 7 days, considered to be the follow-up assessment (FUA), and another at the time of discharge from the hospital, considered to be the final assessment (FA). This can be observed in more detail in Table 1.

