#### Interventions

The conventional standard of care will be maintained in both groups, as well as the lines of treatment prescribed by the Medical Oncology Service of the CAUSA. Additionally, all subjects in both groups will receive an individualised prescription of multimodal physical exercise.

In the experimental group, we will also implement an intervention with a programme for recovering the individual’s autonomy by means of reeducation in the activities of daily living.

The *oncological functional reeducation programme* will comprise the following actions:
Multimodal physical exercise programme: this therapeutic measure will be applied for all individuals, in both the experimental group and the control group. It will consist of two short sessions each day, one in the morning and another in the afternoon, of 15–20 min each. The dose and load of the programme, as well as any special considerations, will always be adapted to the functional capacities of each patient, in accordance with the assessments carried out. Additionally, we will always take into consideration the patient’s symptoms at the time, as there may be individual changes in a very short period of time. The directive will be to maintain a multimodal exercise programme to complete different exercises, including aerobic exercises, balance exercises, and low-load resistance training exercises targeting specific muscle groups, in both the upper quadrant and the lower quadrant. The sessions will be done following the recommendations of the American College of Sports Medicine (ACSM) [23], with an initial warm-up (2–3 min), a main part (8–12 min), and a final cool-down and relaxation (5 min)It will be permitted—and recommended—to do the exercises with the patient’s specific oxygen therapy range, if they have one. The patient’s oxygen saturation levels will also be measured before, during, and after completing the exercise, to ensure that there are no clinical alterations, which may contraindicate the therapeutic practice.Reeducation in the activities of daily living: Intensity and simplification of the activities and trainings of energy-saving techniques (EST). An individual training will be completed on the rules for the simplification of activities, consisting of [24]:

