### Data analysis

The statistical analysis will be carried out with the intention to treat. In the descriptive analysis, the population is described by presenting the data as means and standard deviations for the continuous variables and as frequency distributions for the qualitative variables. To evaluate the comparability in the baseline assessment between the two study groups, we will employ the Chi-squared test for qualitative variables and the Student’s T-test for the comparison of the means between the two groups, in addition to the Kolmogorov–Smirnov test to find the normality of the sample. In the inferential analysis, we will consider a confidence interval of 95% (*p* < 0.05), and will use Student’s T-test for related pre and post samples and for independent samples at the end of the study, in addition to a multivariate analysis of variance (MANOVA) with repeated measures (3 levels) to assess interactions between categorical variables, and to determine significant differences between groups and within groups. Additionally, to assess the magnitude of the change in the variables, the effect size of the interventions will be calculated as Cohen’s d (small (0.2), medium (0.5), and large (0.8)) and the partial eta squared (ƞ2p) (small (0.01), medium (0.06), and large (0.14)), where significant, as appropriate with the statistical test applied [25]. We will use Pearson’s Correlation Coefficient to analyse the correlations between the various intervening variables and the parameters established in the different questionnaires and scales employed. A survival follow-up analysis will be completed using the Kaplan–Meier non-parametric method to learn the time of the intervention until the patient’s discharge from hospital, and the survival curves of each of the groups in the study will be compared using the non-parametric logrank test. Processing and analysing the data will be done using the statistics pack SPSS 25.0.

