## Conclusions

This manuscript presents the protocol of a study aimed at assessing the results of a model of care based on a comprehensive rehabilitation combining a usual multimodal physical exercise programme and a specific programme of recovery of autonomy through activities of daily living training, on functionality, respiratory parameters and quality of life in oncology patients with dyspnea.

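### The effect size of the interventions is not tied to the randomised between-arm contrast and is reported only when significant, so within-arm change could stand in for an intervention effect

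*Protocol article*

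**What the plan says.** The Data analysis section of the protocol article lists three kinds of inferential test: a paired t-test of pre against post, an independent-samples t-test at the end of the study, and a three-level repeated-measures MANOVA for interactions and "to determine significant differences between groups and within groups". It then states that "to assess the magnitude of the change in the variables, the effect size of the interventions will be calculated" as Cohen's d and partial eta squared. Two conditions follow: effect sizes are given where the result is significant, and the measure is chosen to suit the test used. No test is named as the one that answers the aim.

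The Aims section states the hypothesis as an add-on question: does re-education in daily activities increase the benefit obtained from exercise alone? Under Interventions, "The conventional standard of care will be maintained in both groups", and both arms also receive the exercise programme. Under Participants, patients must be in hospital, score 2 or more on the MRC scale and "receive fewer than 85 points on the Barthel Index". The last assessment is at discharge (Evaluations and study plan).

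**The concern.** The trial randomises one thing, the addition of the autonomy programme. Only a comparison between arms isolates it. Change within an arm mixes any effect of that programme with exercise, oncology treatment, standard care, the course of the illness up to discharge, and regression to the mean after selection on poor scores. The text links the magnitude of change to an effect of the interventions and lets each significant test carry its own effect size under that label.

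The significance condition sharpens the problem. If re-education adds nothing, the between-arm test is non-significant in about 95% of trials and yields no effect size. The within-arm effect size appears whenever patients improve enough. The only d, or the only partial eta squared, in the report could then be the uncontrolled one, labelled as an intervention effect. It could be read as support for the programme when the randomised comparison shows none.

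**Working it through.** **1. The plan's own figure.** The Sample size section works "in order to detect a difference greater than or equal to 7.5 units" on the Barthel Index, "accepting an alpha risk of 0.05 and a beta risk of 0.2 in a bilateral contrast", with a common SD of 8.3 and 20% loss.

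- n per arm = 2 × (1.96 + 0.8416)² × 8.3² / 7.5² = 2 × 7.849 × 68.89 / 56.25 = 19.2, rounded up to 20.
- Allowing for loss: 20 / 0.8 = 25 per arm.

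The stated 25 per arm reproduces. It rests on a two-group comparison, so the design is sized for the between-arm question.

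**2. Assumptions for the illustration.** The documents give no expected recovery and no SD of change. I assume:

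- the same mean recovery in both arms, so the true between-arm effect is zero;
- an SD of change of 8.3, borrowed from the Sample size section (it equals the cross-sectional SD when the pre-post correlation is 0.5);
- 20 completers per arm;
- two-sided tests at 0.05;
- the paired test run in the experimental arm.

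**3. Paired test in one arm.** The true d is recovery / 8.3. The noncentrality is d × √20, and the critical t on 19 degrees of freedom is 2.093.

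| Recovery in both arms | d | Noncentrality | Paired test significant |
|---|---|---|---|
| 2.5 points | 0.30 | 1.35 | 25% |
| 5 points | 0.60 | 2.69 | 72% |
| 7.5 points | 0.90 | 4.04 | 97% |

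**4. Joint result with the between-arm test.** Two normal arms were simulated with identical recovery. The between-arm test, whether on final scores or on change, was significant in about 5% of trials throughout, as it should be.

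| Recovery in both arms | Within-arm significant, between-arm not | Within-arm significant and observed d ≥ 0.8 |
|---|---|---|
| 2.5 points | about 23% | about 3% |
| 5 points | about 70% | about 23% |
| 7.5 points | about 93% | about 67% |

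The middle column is the situation in which the reporting rule would show a within-arm effect size and no between-arm one.

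**5. Sensitivity.** With a pre-post correlation of 0.7 (SD of change 8.3 × √0.6 = 6.4), the middle column becomes 36%, 87% and 95%, using the t-test on final scores.

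**6. When a within-arm effect would count as large.** The plan's threshold is d = 0.8. At an SD of 8.3 this needs a mean change of 0.8 × 8.3 = 6.6 points.

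**The case against.** The strongest reply is that the controlled analyses are already there. The same section plans an independent-samples t-test at the end of the study and interaction tests in the MANOVA. These keep their 5% error rate, and because the effect size is matched to the test applied, d and partial eta squared can attach to them as well. This stands. The plan does not define the effect size solely as pre-post change, and an attentive reader of the results would see the null between-arm test.

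It does not remove the problem. Nothing gives the between-arm test precedence, and the significance condition withholds its effect size exactly when it is null.

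A reader might infer several stronger things that the documents do not support:

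- **That ordinary recovery would be reported as a large programme effect.** It could be, but this depends on an unknown recovery. The 7.5 points in the Sample size section is the difference to be detected between groups, not an expected recovery in both. At 2.5 or 5 points an observed large d is uncommon or a minority result. Recovery is not assured either: the Background describes dyspnoea as a possible sign of the final phase of disease, and the withdrawal criteria foresee progression.
- **That the paired test is stated to be run in each arm.** The text does not say so. The within-groups wording belongs to the MANOVA clause and makes that reading plausible. A paired test pooled over arms would say still less about re-education.
- **That the trial means to evaluate the combined programme without a control.** The Conclusions section does describe "assessing the results of a model of care based on a comprehensive rehabilitation combining a usual multimodal physical exercise programme" together with autonomy training. The Abstract and the Aims state the add-on comparison clearly, so this is loose wording and does not change the trial's question.

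**Conclusion.** The concern holds in a limited form. The Data analysis section leaves the effect size of the interventions untied to the randomised contrast, places paired and within-group tests in the inferential analysis, and reports effect sizes only when significant. A within-arm d, or a partial eta squared for time, could therefore be presented as an intervention effect while the between-arm effect is null and has no effect size reported. Under the assumptions above, the conditions for this arise in about 23% to 93% of trials as common recovery goes from 2.5 to 7.5 points. The range shows how strongly the answer depends on a recovery the documents do not give. The planned between-arm tests are sound and the sample size is unaffected. The defect lies in labelling and reporting. It should be corrected because it bears directly on what the trial can claim.

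**What to change.** In the Data analysis section:

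1. Define the effect size of the intervention on the between-arm contrast only: Cohen's d for experimental minus control at the same assessment, and partial eta squared for the group-by-time interaction.
2. Report it with a 95% CI whether or not the test is significant, and drop the significance condition.
3. Present within-arm change as descriptive, with mean and 95% CI, and state that it is not evidence of an intervention effect. This covers the partial eta squared for time as well as the paired d.

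The cost is a few sentences. The 25 per arm stays as it is, because it already rests on a between-group comparison. The small downside is losing the within-arm p-values as inferential results.

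### Effect sizes are calculated only where the test is significant, so reported standardised effects are biased upward and non-significant comparisons carry none

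*Protocol article*

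**What the plan says.** The Data analysis section sets out the tests first: "Student’s T-test for related pre and post samples and for independent samples at the end of the study", plus a repeated-measures MANOVA with three levels. It then turns to magnitude: "to assess the magnitude of the change in the variables, the effect size of the interventions will be calculated" as Cohen's d or partial eta squared. Benchmarks are given for both: "Cohen’s d (small (0.2), medium (0.5), and large (0.8") for d, and "small (0.01), medium (0.06), and large (0.14") for partial eta squared. The sentence closes with the condition "where significant, as appropriate with the statistical test applied".

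Two other statements in the section bear on the point. The descriptive analysis involves "presenting the data as means and standard deviations for the continuous variables". For the inferential analysis, "we will consider a confidence interval of 95"%, followed in brackets by p < 0.05. The interval is thus set beside the significance level and is not attached to a between-group difference.

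The Sample size section gives 25 per group, a Barthel Index difference of 7.5 points, a common standard deviation of 8.3 and 20% loss to follow-up, "accepting an alpha risk of 0.05 and a beta risk of 0.2 in a bilateral contrast".

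**The concern.** The stated purpose of the effect sizes is to describe magnitude. An estimate of magnitude that is computed only when it has passed a significance threshold is a selected estimate, and its expected value lies above the true effect. In a trial of this size the threshold is high, so the selection is strong for any outcome whose true effect is small or moderate. The trial was sized on the Barthel Index alone. SPPB, TSK-F, oxygen saturation and ECOG status have no such planning, so the distortion may be greatest for them.

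Comparisons that miss significance would have no standardised effect size beside them. The effect-size column of the results would then show only the comparisons that passed, and only estimates on the high side. This is a rule that the protocol states, not a detail left to a fuller document.

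**Working it through.** **Inputs.** Sample size section: difference 7.5, SD 8.3, two-sided alpha 0.05, power 0.80, 25 per group, 20% loss. Data analysis section: the tests, the benchmarks and the significance condition.

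**The plan's own figure.** Normal approximation: n = 2 × (1.960 + 0.842)² × (8.3/7.5)² = 19.2, so 20 per arm; 20/0.8 = 25 per arm. The stated 25 is reproduced. The planned standardised effect is 7.5/8.3 = 0.904. The two cases used below are 25 per arm (no loss) and 20 per arm (20% loss).

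**Smallest effect that can be reported under the rule.**
- Between groups, |d| = t(0.975, 2n−2) × √(2/n). With 20 per arm: 2.024 × 0.316 = 0.640, or 0.640 × 8.3 = 5.3 Barthel points. With 25 per arm: 2.011 × 0.283 = 0.569, or 4.7 points.
- Within group, taking d as the mean change over the SD of change, dz = t(0.975, n−1)/√n. With 20: 2.093/4.472 = 0.468. With 25: 2.064/5 = 0.413.
- Partial eta squared = F·df1/(F·df1 + df2) at the 5% critical F. With 20 per arm: 0.097 (df 1, 38), 0.076 (df 2, 76), 0.150 (multivariate, df 2, 37). With 25 per arm: 0.078 (df 1, 48), 0.061 (df 2, 96), 0.120 (multivariate, df 2, 47).

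On the protocol's scale, a small between-group d (0.2 up to 0.5) cannot be reported in either case. A within-group d can still fall just inside that band.

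**Average reported d for the end-of-study comparison.** 400,000 simulated trials per scenario, normal outcome, common SD, equal arms:

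| True d | Per arm | Significant | Mean d, all trials | Mean d, significant only | Significant results with \|d\| < 0.8 |
|---|---|---|---|---|---|
| 0.2 | 20 | 9.4% | 0.21 | 0.72 | 61% |
| 0.2 | 25 | 10.6% | 0.20 | 0.66 | 80% |
| 0.5 | 20 | 34.0% | 0.51 | 0.87 | 45% |
| 0.5 | 25 | 40.9% | 0.51 | 0.79 | 62% |
| 0.904 | 20 | 79.7% | 0.92 | 1.04 | 21% |
| 0.904 | 25 | 87.8% | 0.92 | 0.98 | 27% |

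**Inflation (mean of significant results divided by true d).** At 0.2: 3.6 (20 per arm) and 3.3 (25 per arm). At 0.5: 1.7 and 1.6. At 0.904: 1.04/0.904 = 1.15 and 0.98/0.904 = 1.08, about 1.1. Without the filter the mean stays close to the truth throughout.

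**Chance that no between-group effect size is reported.** At 0.904: 1 − 0.797 = 20% and 1 − 0.878 = 12%. At 0.5: 66% and 59%.

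**The case against.** **The phrase may only match the index to the test.** This reading is possible but less natural. The second half of "where significant, as appropriate with the statistical test applied" already does the matching, and on this reading the first two words would have no function. If matching is what was meant, deleting those words makes the text say so.

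**A reader might infer that every reported effect will be large.** The protocol's own scale does not support that. Large starts at 0.8. The between-group floor of 0.57 to 0.64 is medium, and the within-group floor of 0.41 to 0.47 is below medium. With 25 per arm, about 80%, 62% and 27% of significant results would have |d| below 0.8 at true d of 0.2, 0.5 and 0.904. The effects are inflated, but not all are large.

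**A reader might infer that null results carry no estimate at all, and that later meta-analyses inherit the bias.** Neither follows. Means and standard deviations are planned for continuous variables, and the Data Availability section offers the datasets on request. Group means, SDs and numbers allow a difference and a d to be computed whatever the p-value. What is missing is the standardised effect size. The text also does not commit to a confidence interval for the between-group difference, although it does not exclude one.

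**The effect on the main planned comparison is small.** This stands: about 1.1-fold at the planned effect. The rule alters no test or p-value.

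**Cohen's d does not suit every outcome.** This also stands. MRC dyspnoea has five grades and ECOG is a graded performance status, so the remedy should not impose d on them.

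**Conclusion.** The point holds as a reporting defect. The condition biases the standardised effects that are reported and removes them from non-significant comparisons. The bias is slight if the Barthel effect is as large as planned (0.904 reported on average as 1.04 to 0.98). It is material if a true effect is moderate (0.5 reported as 0.87 to 0.79) and more than threefold at 0.2. At the planned effect, about one trial in five (20 per arm) to one in eight (25 per arm) would give no between-group effect size for the Barthel Index.

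These figures assume equal arms, normal outcomes with a common SD, and the two-sample t-test at the end of the study. The true effects of 0.2 and 0.5 are the protocol's small and medium benchmarks, used as illustrations and not as forecasts. The validity of the tests and the sample size are not in question here. The change should be made before the analysis, because the rule distorts the quantity that the effect sizes are meant to convey.

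**What to change.** Delete the first two words of "where significant, as appropriate with the statistical test applied", so that the clause only ties the index to the test. Add that, for each primary and secondary outcome and whatever the p-value, the report will give:

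- the between-group difference with its 95% confidence interval;
- the effect size that matches the test used, with its 95% confidence interval: Cohen's d or partial eta squared, or an ordinal measure for graded scales such as MRC and ECOG.

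The cost is a few more table cells. No test, sample size or study procedure changes. With 25 per arm, the mean reported d would then be about 0.20, 0.51 and 0.92 for true values of 0.2, 0.5 and 0.904.

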#### Description of the variables

For the principal variable being manipulated, we will study dyspnoea (Medical Research Council, MRC) and the degree of dependence in carrying out the activities of daily living (Barthel Index, BI). And as secondary variables, we have the patient’s physical performance (via the Short Physical Performance Score, SPPB), their fear/avoidance of movement (Tampa Scale of Kinesiophobia–Fatigue, TSK-F), the oxygen saturation in the blood (pulse oximetry), and the quality of life of the oncology patient (ECOG performance status scale). Other intervening variables include those gathered from the patient’s clinical history, such as pathological diagnosis, number of lines of treatment, and socio-demographic and anthropometric data (sex, age, weight, height, and BMI).

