#### Tools employed in the evaluation of the variables

“Barthel Index, (BI)” [18]: to evaluate dependence. Measures physical disability with proven validity and reliability. It is easy to apply and to interpret. Useful for evaluating the patient’s functional independence in the activities of daily living (ADL). Scored from 0 to 100, it quantifies the individual’s degree of dependence.“Medical Research Council dyspnoea scale (MRC)” [19], to evaluate dyspnoea. The aim is to make it possible for the patients to quantitatively grade their own dyspnoea in a simple, visual manner. It establishes 5 degrees of dyspnoea when carrying out activities.“Short Physical Performance Score (SPPB)” [20], to evaluate physical performance. The short physical performance battery, proven in our area for primary health care, is a test designed specifically to predict disabilities, and it has demonstrated the capacity to predict adverse events, dependence, institutionalisation, and mortality.The “Tampa Scale of Kinesiophobia–Fatigue (TSK-F)” [8, 9], was developed to evaluate the fear of movement related to fatigue/pain. It has been proven effective in oncology patients and those with chronic fatigue syndrome. We will use the model with 11 items (TSK-F-11).“Pulse oximetry” [21]: a non-invasive technique which uses a pulse oximeter to measure the saturation of oxygen (Sat O_2_) in the haemoglobin in circulating blood, usually in arterial blood.“ECOG performance status scale” [22], is a practical way to measure the quality of life of cancer patients, whose life expectancies may change within a period of months, weeks, or even days. It was designed by the Eastern Cooperative Oncology Group (ECOG) in the United States and validated by the World Health Organization (WHO). The primary function of this scale is to objectify the patient’s quality of life or performance status.

The variables will be recorded on an individual sheet for each patient and stored afterwards in a database designed specifically for this study.

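### Pearson's correlation is specified without exception for a set of variables that includes pathological diagnosis, where the coefficient depends on arbitrary category codes

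*Protocol article*

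**What the plan says.** Three places in the protocol article bear on this.

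- **Data analysis.** The only association method named is Pearson's "Correlation Coefficient to analyse the correlations between the various intervening variables and the parameters established" in the questionnaires and scales. The sentence has no exception and offers no alternative.
- **Description of the variables.** Intervening variables is the protocol's own term. They include items from the clinical history, "such as pathological diagnosis, number of lines of treatment, and socio-demographic and anthropometric data (sex, age, weight, height, and BMI").
- **Participants.** "Participants must have a pathological diagnosis of an oncological disease". No tumour type is specified and no grouping of diagnoses is given.

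The Data analysis section does separate variable types elsewhere. Qualitative variables are described by frequencies, and for baseline comparability "we will employ the Chi-squared test for qualitative variables", with a t-test for means. The correlation sentence does not carry that separation over.

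**The concern.** Pearson's r needs numbers. Age, weight, height, BMI and number of treatment lines supply them. Pathological diagnosis does not: its numbers would be labels chosen when the database is built. With more than two unordered categories, renumbering the labels changes the strength of the linear relation, its direction and its p-value, although the patients and their scores are the same.

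A published statement that tumour type is, or is not, correlated with Barthel, MRC or SPPB would therefore partly describe the coding sheet. Two teams with identical data could report opposite signs, or one could report an association and the other none.

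**Working it through.** **The plan's own figure.** The only computed figure in the article is the sample size, which this point does not touch. It reproduces: 2 × [8.3 × (1.960 + 0.842) / 7.5]² = 19.2, so 20 per group, and 20 / 0.8 = 25 per group after 20% loss. (A t-based calculation gives 21, then 27.) I borrow n = 50 and the SD ("The assumed common standard deviation is 8.3") for the illustration. That SD was assumed for the two-arm comparison, not within diagnoses.

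**Assumptions.** The article gives no number of diagnoses, no distribution and no score difference between them. What follows is assumed: five diagnoses of 10 patients each, within-group SD 8.3, and mean Barthel scores of 50, 56, 62, 53 and 59.

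**An answer that does not depend on coding.**
- Grand mean 56; deviations -6, 0, +6, -3, +3.
- Between-group sum of squares: 10 × (36 + 0 + 36 + 9 + 9) = 900.
- Within-group sum of squares: 45 × 8.3² = 3100.05. Total: 4000.05.
- Eta squared = 900 / 4000.05 = 0.225.
- F = (900 / 4) / (3100.05 / 45) = 225 / 68.89 = 3.27, p = 0.020.

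**Pearson's r on the same data.** With codes 1 to 5, the sum of squares of the codes is 10 × (4 + 1 + 0 + 1 + 4) = 100. So r = 10 × Σ(code - 3)(deviation) / √(100 × 4000.05) = 10 × Σ / 632.46.

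| Codes given to the five diagnoses | Σ | r | p |
|---|---|---|---|
| 1, 3, 5, 2, 4 | 12 + 0 + 12 + 3 + 3 = 30 | +0.47 | 0.0005 |
| 2, 4, 1, 3, 5 | 6 + 0 - 12 + 0 + 6 = 0 | 0.00 | 1.0 |
| 5, 3, 1, 4, 2 | -30 | -0.47 | 0.0005 |

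Over all 120 codings, 42 give p < 0.05 (|r| above 0.279 at n = 50).

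**Fewer groups.** With three diagnoses (17, 17 and 16 patients; assumed means 50, 57.5 and 53), the six codings give r = ±0.15 (p = 0.31), ±0.22 (p = 0.13) or ±0.36 (p = 0.011). ANOVA gives one answer. The grand mean is 53.51, the between-group sum of squares 484.2 and the within-group sum of squares 47 × 68.89 = 3237.8. Hence eta squared = 484.2 / 3722.1 = 0.13, F = 3.51, p = 0.038.

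**Repeated samples.** Simulated sets of 50 patients with five equally likely diagnoses, base mean shifts 0, +6, -4, +3, -6, all 120 codings. Figures given as ranges come from separate runs.

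| Assumption | Average extremes of r | Codings with p < 0.05 | ANOVA p < 0.05 |
|---|---|---|---|
| Base shifts, SD 8.3 | about ±0.50 | 33–35% | 79–83% |
| Shifts halved, SD 8.3 | about ±0.34 | 14–16% | 24–30% |
| Base shifts, SD 15 | about ±0.36 | 16% | 28–29% |
| No true differences | about ±0.26 | 4.9% | 4.5% |

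The symmetry of the extremes is automatic, because reversing any coding flips the sign. The informative columns are the last two.

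**Binary sex.** Splitting the five-group data into two groups and swapping the codes gives r = ±0.27 with p = 0.054 both ways, equal to the pooled t-test p-value. Only the sign is arbitrary, and it is readable once the coding is stated.

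**The case against.** The best defence is that nobody intends to number tumour types. The article does not say so; the reading joins the correlation sentence to an illustrative list in another section. The Data analysis section separates qualitative from continuous variables twice and names a repeated-measures MANOVA for interactions between categorical variables. One could therefore take Pearson's coefficient to be meant for the numeric intervening variables only. The article is also condensed, and the pairing of coefficients with variables might sit in a fuller document.

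This shows that the slip may be one of wording, but it does not remove it. The Chi-squared clause covers baseline comparability, and the MANOVA clause covers the group and time analysis. Neither covers the association of diagnosis with the scales. The correlation sentence uses the protocol's defined term, whose first listed member is pathological diagnosis, and makes no exception. A method is stated that does not suit one of its stated inputs; this is not a detail left open.

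Four stronger readings are tempting, and the article does not support them:

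- **Pearson's r is wrong for the whole set.** The text refers to the various intervening variables, not to all of them. The coefficient is legitimate for the numeric ones and valid for sex as a point-biserial r.
- **The ordinal scales make it invalid.** For the MRC, "It establishes 5 degrees of dyspnoea when carrying out activities", and ECOG is also graded. Spearman's coefficient for these, or for number of treatment lines, is a preference and not the correction of an error.
- **False associations will multiply.** With no true differences, 4.9% of codings were significant, which is the nominal rate.
- **The number of correlations is the problem.** Multiplicity is a separate matter. A count over all six outcomes would also include pulse oximetry, which the article describes as a technique, while the sentence is limited to questionnaires and scales.

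**Conclusion.** The point holds for one variable. As written, the plan applies Pearson's r to pathological diagnosis. If diagnosis is recorded in more than two categories, the resulting coefficient, sign and p-value are uninterpretable, and a real association can be missed. That conclusion depends only on diagnosis being nominal with more than two levels, which the eligibility criteria allow.

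The size is illustrative. Under the assumed five groups, r spans about -0.5 to +0.5 and roughly a third of codings are significant, where ANOVA detects the difference about 80% of the time. Smaller differences or a larger SD shrink both figures. The harm is lost meaning and lost power, not excess false positives.

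The consequence is minor. This is a secondary association analysis, and the between-group comparison of Barthel and MRC, the sample size and the treatment conclusion do not depend on it.

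**What to change.** Replace the correlation sentence in the Data analysis section with wording to this effect: Pearson's coefficient will be used for the numeric intervening variables (age, weight, height, BMI, number of lines of treatment) and, as a point-biserial coefficient with its coding stated, for sex; pathological diagnosis, in groups defined before the analysis, will be related to the scale scores by one-way ANOVA or Kruskal-Wallis with eta squared; these analyses are exploratory.

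Spearman's coefficient may be added where MRC, ECOG or number of treatment lines is involved, but this is optional.

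The cost is one sentence and a short list of diagnosis groups. The SPSS package already named covers the methods, and no change to data collection, sample size or the primary analysis is needed.
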